
**Fig. 1 Fig1:**
[figure not shown]
Power curve for simulation 1 assuming of balanced clusters (equal number of patients included per center)

However, in practice, unequal number of patients is expected to be included by each center. Also, seasonal effects should be accounted for in the analysis. Therefore, a second simulation was conducted in a similar way. The number of patients included per center was (roughly) based on the number of eligible patients in the past year (known for 4 hospitals) divided by 2 (assuming that 50% of eligible patients would participate). Inclusion rates for the two hospitals for which this was not known were set equal to the hospital with lowest inclusion rate, resulting in monthly inclusions of 13, 7, 7, 1, 1, 1. Seasonal effects were included by a monthly effect, which were assumed to follow a sine function with a period of 12 months. The SD of the seasonal effects over a 12-month period was set equal to the between cluster SD. The half period (*x* = *π*) was set equal to the moment of cross-over. For sample sizes varying from 60 (two months of inclusion) to 360 (12 months of inclusion), again 5000 simulations were run for each sample size considered. Linear mixed models were fitted including center as random effect and month and treatment as fixed effects. Using a two-sided alpha of 5%, *n* = 120 patients total (rounded to above) would be required in total to demonstrate non-inferiority with a power of 80% (Fig. 2). Accounting for a 10% loss to follow-up, a total of *n* = 134 patients will be included. It should be noted that in the simulations, it was assumed that only one VAS pain will be collected for each patient, while in reality multiple VAS scores (one per day) will be obtained during the period between the visit to the emergency department and the operation. An average VAS pain for each patient will be estimated by a multilevel linear mixed model using random intercept for patient nested within center. Including this aspect in the simulation studies was deemed too complicated, since no reliable estimates for the correlation between daily VAS pain scores in this setting are available. However, following the reasoning that multiple measures will lead to a more precise estimate than a single measure, it can be expected that in practice a higher power will be achieved compared to the simulations and including this is not strictly necessary (i.e., the simulations can be regarded as conservative in this respect).

**Fig. 2 Fig2:**
[figure not shown]
Power curve for simulation 2 assuming unbalanced clusters (unequal number of patients included per center) and adjustment for seasonal effects

In the Maasstad Hospital, approximately 590 adult patients are diagnosed with a DRF per year. According to Brogren and colleagues, approximately 350 (60%) will be displaced [5].

However, not all of these patients will have CR followed by surgical treatment. Assuming that 60% of all patients with a displaced DRF will meet the inclusion criteria, combined with a rejection rate of 30%, we estimate to require 13 months for inclusion in case of a single-center design. Assuming that the average amount of inclusions per month in the other participating centers equals the amount in the Maasstad Hospital, we can divide the required time by the amount of centers. With a total of six participating centers, we estimate to require 3 months to complete the inclusion. Combined with a follow-up time of 12 months and 3-month margin, the total required time for the clinical part of the trial will be 18 months.

### Recruitment {15}

Eligible patients at the ED, fit to the inclusion and exclusion criteria, will be informed about the study and invited to participate by the treating physician. The patient will also receive written information on the study and will have the opportunity to ask questions on before making the decision to participate or not. However, this needs to be done in a short period of time (approximately 30 min) because of the acute problem presentation and setting. If the patient fits the inclusion and exclusion criteria and signs the informed consent form, baseline information will be recorded.

## Assignment of interventions: allocation

### Sequence generation {16a}

Randomization at patient level will be challenging because of the 24/7 availability of the ED in all participating hospitals and therefore the 24/7 availability to include possible candidates. To overcome potential protocol violations and unnecessary loss of potential inclusions, randomization will take place as a cluster per hospital with a cross-over point halfway the needed inclusions per hospital (i.e., after 20 inclusions). This means that patients presenting at the same hospital will receive the same intervention, and halfway this will change to the other intervention (CR or withholding from CR). Using a simple script in R statistics, starting treatment will be randomly decided for each hospital, with guarantee that both treatments will occur three times.

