**Methods:**

In this multicenter randomized clinical trial, we will randomize between closed reduction followed by plaster casting and only plaster casting. Patients aged 18 to 75 years, presenting at the emergency department with a displaced distal radial fracture and requiring surgery according to the attending surgeon, are eligible for inclusion. Primary outcome is pain assessed with daily VAS scores from the visit to the emergency department until surgery. Secondary outcomes are function assessed by PRWHE, length of stay at the emergency department, length of surgery, return to work, patient satisfaction, and complications. A total of 134 patients will be included in this study with follow-up of 1 year.

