### Trial design {8}

This trial is designed as a non-inferiority multicenter cluster randomized trial. Participants will be equally distributed between the two treatment arms.

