### Sample size {14}

The sample size calculation is based on our primary outcome parameter: the VAS score for pain reported on a daily basis from the visit to the ED until the day of surgery. To find out if the pre-operative pain scores of patients that are refrained from CR are comparable with the scores of the CR group, we will use a non-inferiority test. This requires a non-inferiority margin, which is the biggest difference between the two groups in favor of the CR group, without a statistical difference [28]. The European Medicines Agency advices to base the non-inferiority margin on a difference that is not clinically important [29]. Therefore, our non-inferiority margin is 50% of the minimal clinical important difference (MCID) of the VAS [28]. Based on a systematic review concerning the MCID of VAS scores, a MCID is a context-specific and methodological dependent value [30]. To the best of our knowledge, the MCID of the VAS score for DRFs is unknown. Therefore, we used the MCID of a study that included trauma patients with isolated acute extremity pain [31]. For the description of the MCID of the VAS score, the VAS scale is seen as a 100 mm line. With an MCID of 19.3 mm, our non-inferiority margin will be 9.7 mm (= 50%). As only Bird et al. provide a standard deviation (SD) around the MCID, we will use that value of 15 mm for our sample size calculation [24]. To correct for a cluster-effect we use an intra-cluster correlation (ICC) coefficient between the different hospitals of 0.06, which is generally reported in the literature for hospital processes. To calculate the required sample size, two simulations were run both assuming a fixed number of six clusters (hospitals). In the first simulation, an equal number of subjects per hospital was assumed. Hospitals were randomized to start with treatment A (3 centers) or B (3 centers) in a 1:1 fashion and crossed over after half of the patients were included. For total sample sizes varying from 12 to 502 with increments of 12, 5000 simulations were run for each sample size considered. In each simulation, random data was generated under the specifications described above. A linear mixed model was fitted with a random intercept for cluster and treatment group as fixed effect. A 95% confidence interval was calculated based on the t-distribution with degrees of freedom estimated by the Satterthwaite method. The power was calculated as the percentage of simulations in which the upper limit of the 95% confidence interval was smaller than the non-inferiority margin. From the first simulation, it followed that, using a two-sided alpha of 5%, *n* = 80 patients total would be required in total to demonstrate non-inferiority with a power of 80% (Fig. 1).

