## Trial status

The RECORDED trial with protocol version 2.0 dating February 10, 2023, was accepted by the ethics committee on January 27, 2023. The first inclusion was on June 23, 2023, and recruitment is expected to be completed in April 2024.

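### The crossover count of 20 per hospital is not halfway for six hospitals sharing 134 patients, so the written rule departs from the half-and-half crossover used for the power calculation

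*Protocol article*

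**What the plan says.** Sequence generation {16a} allocates treatment by hospital, "with a cross-over point halfway the needed inclusions per hospital (i.e., after 20 inclusions". Three hospitals start with each treatment.

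The other design statements are:

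- **Total.** The abstract gives the size: "A total of 134 patients will be included in this study". Sample size {14} reaches it from 120 patients plus 10% loss to follow-up.
- **Clusters.** Both simulations were run "assuming a fixed number of six clusters (hospitals".
- **Crossover as simulated.** In the first simulation hospitals "crossed over after half of the patients were included". The second was run in a similar way, with the crossover placed at the half period of the seasonal curve.
- **Recruitment.** The second simulation uses unequal rates, "resulting in monthly inclusions of 13, 7, 7, 1, 1, 1". The feasibility paragraph at the end of the same section instead assumes the same monthly rate in all six hospitals.
- **Balance.** Trial design {8} states: "Participants will be equally distributed between the two treatment arms".
- **Duration.** Trial status gives a first inclusion in June 2023, and "recruitment is expected to be completed in April 2024".

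**The concern.** The count of 20 is presented as the halfway point, and it is the only number a hospital could act on. If it does not fit the total, hospitals following it will not deliver both treatments in equal halves.

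The crossover is what separates the treatment effect from differences between hospitals in this open-label trial with six clusters. A hospital that never switches contributes no within-hospital comparison. A hospital that switches very late contributes little. The simulated power assumes that every hospital switches at its midpoint. Once recruitment has ended, a missed crossover cannot be restored.

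**Working it through.** **The plan's own figures.** 120/0.9 = 133.3, rounded up to 134, which agrees with the article. The 80 patients of the first simulation also reproduce: 81% power if the 15 mm SD is residual, 84% if it is total. The 120 of the second simulation is not reproduced exactly (a reconstruction gives about 89% at 120). The article says that it rounded up and does not give the variance details, so 120 is not called wrong here.

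**Does 20 fit 134?**

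- Halfway at 20 means 2 × 20 = 40 per hospital, and 6 × 40 = 240. That is 106 more than 134.
- 134/40 = 3.35, so at most three hospitals could reach 40.
- All six reaching 20 uses 6 × 20 = 120 patients and leaves 14 for all post-crossover periods together.

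**Equal recruitment.** 134/6 = 22.3 per hospital, so halfway is about 11. Crossing after 20 gives a split of 20 to 2 or 3.

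The effect on precision can be worked by hand for 22 per hospital (132 in total), with a random intercept for hospital:

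- Total variance is 15² = 225. With ICC 0.06 the between-hospital variance is 13.5 and the residual variance 211.5.
- With treatment coded ±½ and three hospitals starting each arm, 1/SE² = 6 × [n/4 − λS²]/211.5. Here λ = 13.5/(211.5 + 13.5n), and S is half the difference between the two period sizes.
- Halfway (11/11): S = 0, so 1/SE² = 6 × 5.5/211.5 = 0.156 and SE = 2.53 mm.
- After 20 (20/2): S = 9 and λ = 13.5/508.5 = 0.0265, so 1/SE² = 6 × (5.5 − 2.15)/211.5 = 0.0950 and SE = 3.24 mm.
- Power = Φ(9.7/SE − 1.96): Φ(1.87) = 97% halfway, and Φ(1.03) = 85% after 20.

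A simulation at 134 with Satterthwaite degrees of freedom gives the same 97% and 85%. The arms stay balanced, because three hospitals start each treatment.

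**Rates 13, 7, 7, 1, 1, 1.** The total is 30 per month, so 134 takes 134/30 = 4.47 months.

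| Rate per month | Expected patients | Own halfway | Split if crossing after 20 | Months to reach 20 |
|---|---|---|---|---|
| 13 | 58 | 29 | 20 / 38 | 1.5 |
| 7 (two hospitals) | 31 | 16 | 20 / 11 | 2.9 |
| 1 (three hospitals) | 4–5 | 2 | 4–5 / 0 | 20 |

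Even over the roughly 10 months to April 2024, a hospital including 1 per month reaches about 10, not 20.

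Arm sizes depend on which hospitals start with which treatment. Take sizes 58, 31, 31, 5, 5 and 4. If the large hospital and two small ones (5 and 4) start with one arm, that arm receives 20 + 11 + 11 + 5 + 4 = 51 and the other 83. The reverse sequence gives 83:51. Crossing at each hospital's own half gives between 66:68 and 68:66.

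Averaged over the 20 possible starting sequences:

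- Random-intercept model, 132 patients: SE goes from 2.53 to 2.65 mm, and power from about 97% to about 96%.
- With fixed month effects added, 134 patients: power goes from about 93% to about 90%.

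**The case against.** The strongest reply is that halfway is the governing rule and 20 a loose parenthesis. The section states the halfway principle twice, and it agrees with the simulations. This stands in part: the repair is one number, not a redesign. But the count is given as the meaning of halfway, not as an example. The article gives no per-hospital target from which a site could derive another count. Nor is this detail left to a fuller document: two stated numbers are incompatible.

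A reader might infer more than the article supports:

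- **That the trial becomes underpowered.** It does not on average. Power at 134 is about 85% with equal recruitment; with 10% lost (18 before and 2 after crossover per hospital) it is about 83%. A simulated 43% arises only if equal recruitment stops at 120 with nobody included after crossover, which is not the plan. In the month-adjusted model some starting sequences fall below 80%, but they do so under either rule (lowest 74% at own half, 69% after 20).
- **That both harms occur together.** They belong to different scenarios. Where hospitals fail to cross, the power loss is small; where the power loss is larger, all six cross and the arms stay balanced.
- **That three hospitals will certainly never switch.** The rates are described as rough, and those of two hospitals were unknown and set to the lowest known rate. At these rates the three small sites supply only about 3 × 4.47 = 13 of the 134 patients.
- **That 240 patients are needed.** Nothing in the article supports that total; 240 only shows that the count does not fit.

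**Conclusion.** The contradiction is certain and rests on arithmetic alone: 20 per hospital cannot be halfway when six hospitals share 134 patients, under either recruitment assumption in the article. As written, the rule departs from the crossover on which the power was simulated. At the unequal rates it can also break the equal distribution stated in Trial design {8}, and it confounds treatment with hospital at sites that never switch.

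The cost is moderate. Power falls by about 12 points with equal recruitment and by about 1 to 3 points on average at the unequal rates. The power figures assume SD 15 mm, ICC 0.06, a 9.7 mm margin, no true difference, and one value per patient, as in the article's simulations. The case for correction is that the allocation rule cannot be carried out as described, not that the planned 80% is lost.

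**What to change.** In Sequence generation {16a}, replace the count of 20 with one of these:

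- a halfway count for each hospital from its expected share of 134: about 29, 16, 16 and 2 to 3 at the simulated rates, or about 11 each if equal recruitment is expected; or
- one common crossover date at the expected midpoint of recruitment. With constant rates this coincides with each hospital's own half.

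Either choice brings the rule into line with Trial design {8} and Sample size {14}. If sites have already recruited past that point, report the actual split by arm for each hospital and keep hospital in the primary model.

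The cost is a short amendment and a notice to six hospitals, with no additional patients.

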### Concealment mechanism {16b}

Since this trial will not be blinded, there are no concealment mechanisms. We use a simple algorithm to randomly pick A (closed reduction) or B (no closed reduction) six times and allocate treatment by order of hospital recruitment.

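### Starting treatment is balanced by number of hospitals, not expected inclusions, so about one permitted draw in ten would leave treatment poorly separated from calendar month (minor)

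*Protocol article*

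**What the plan says.** Sequence generation {16a} randomizes whole hospitals, each crossing to the other treatment halfway. The restriction is that "starting treatment will be randomly decided for each hospital, with guarantee that both treatments will occur three times". The switch is placed at a "cross-over point halfway the needed inclusions per hospital (i.e., after 20 inclusions" for each hospital. Concealment mechanism {16b} describes the same draw as follows: "We use a simple algorithm to randomly pick A (closed reduction) or B (no closed reduction) six times and allocate treatment by order of hospital" (that is, the order in which hospitals joined). Neither section mentions hospital size.

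Sample size {14} expects very unequal hospitals, "resulting in monthly inclusions of 13, 7, 7, 1, 1, 1". The rates are described as rough. They were known for four hospitals, and the other two were given the lowest known rate. The section also says: "Also, seasonal effects should be accounted for in the analysis". In the second simulation the season is a 12-month sine. On its size: "The SD of the seasonal effects over a 12-month period was set equal to the between cluster SD". Its half period "was set equal to the moment of cross-over". The model there has center as random effect and month and treatment as fixed effects, and n=120 is given for 80% power.

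Statistical methods {20a} compares the groups with an unpaired t-test or Mann–Whitney test and names no month or center term for that comparison.

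**The concern.** Every hospital gives both treatments, so the arms stay about equal in size whatever the draw. What the draw decides is how well treatment is separated from calendar time. When the sequence starting with closed reduction and the sequence starting without it hold similar numbers of patients, each period contains both treatments equally. When most patients are in one sequence, one treatment is given mainly before the switch and the other mainly after it.

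A 3:3 split of hospitals secures balance in patients only if hospitals are similar in size, and on the plan's rates one hospital supplies 13 of 30 patients and three supply 27 of 30. In a lopsided draw, a month-adjusted analysis loses precision because the estimate leans on the few patients in the smaller sequence. An analysis without month lets the seasonal shift into the treatment difference.

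**Working it through.** **Inputs** (all from Sample size {14}): SD 15 mm, ICC 0.06, margin 9.7 mm, two-sided alpha 5%, rates 13, 7, 7, 1, 1, 1 (total 30 per month), n=120, which is 4 months at 30 per month. Assumption, as in the second simulation: all hospitals switch at about the same time, here after month 2.

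**The plan's own figures.** For the first simulation, a noncentral-t calculation with SD 15 and margin 9.7 gives 81.5% power at 80 patients, so n=80 is reproduced. Also 120/0.90 = 133.3, rounded up to 134. For the second simulation, the month-adjusted calculation below, averaged over all permitted draws, gives 63% at n=60, 80% at n=90 and 89% at n=120. This fits 120 if sample size rose in two-month steps, but the step is not stated. The 5,000-run simulations with Satterthwaite degrees of freedom were not rerun.

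**Enumeration.** There are C(6,3) = 20 draws. Monthly inclusions by sequence:
- 15:15 when the largest hospital is opposite both mid-size ones: 6 draws (30%).
- 21:9 when the largest is with one mid-size and one small hospital: 12 draws (60%).
- 27:3 when the three larger hospitals are together: 2 draws (10%).

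The treatment–period correlation is rho = (n1 − n2)/(n1 + n2), so |rho| is 0, 12/30 = 0.4 and 24/30 = 0.8.

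**Month in the model.** Residual SD = 15 × √0.94 = 14.54 mm. Each hospital gives both treatments equally, so SE = 14.54 × √(4/120) / √(1 − rho²), with power from the noncentral t on 110 degrees of freedom.

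| Split | Draws | SE (mm) | Power at n=120 |
|---|---|---|---|
| 50:50 | 6 | 2.66 | 95% |
| 70:30 | 12 | 2.66/√0.84 = 2.90 | 91% |
| 90:10 | 2 | 2.66/√0.36 = 4.43 | 58% |

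Average: (6 × 0.952 + 12 × 0.913 + 2 × 0.584)/20 = 0.892. A Monte Carlo check with fixed center and month effects gave about 95%, 91% and 58%, and a false non-inferiority rate at the margin near 2.5% for every split.

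**Month not in the model.** Between-cluster SD = 15 × √0.06 = 3.67 mm, so the sine amplitude is 3.67 × √2 = 5.20 mm. Over 4 months, h = π × 2/6 = 1.047. The mean shift between periods is 2 × 5.20 × (1 − cos h)/h = 10.39 × 0.477 = 5.0 mm. The shift in the treatment difference is |rho| × 5.0, which is 0 mm (50:50), 2.0 mm (70:30) or 4.0 mm (90:10), in either direction. When it favors no reduction, the simulated false non-inferiority rate of an unadjusted t-test at the margin was about 10% (70:30) and 31% (90:10).

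**Sensitivity to the placeholder rates** (my assumption: the two unknown hospitals recruit 2, 4 or 7 per month, n=120). The worst split becomes 27:5 (84:16), 27:9 (75:25) or 27:15 (64:36), with month-adjusted power of about 75%, 88% or 93%.

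**The stated switch point.** Twenty inclusions before the switch imply 40 per hospital and 6 × 40 = 240 patients, not 134. At the planned rates, 20 inclusions take 20/13 = 1.5 months, 20/7 = 2.9 months or 20 months. Equal quotas would give 50:50 by sequence in every 3:3 draw, but not at a common date.

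**The case against.** The strongest reply is that the sample size already allows for this. The second simulation uses these unequal rates, a season that reverses at the switch, and a month term. If it drew hospitals 3:3 as the first did, its power averages over the very draws at issue. That largely stands: 18 of the 20 draws keep at least 91% power, and the average of 89% exceeds the planned 80%. What remains is that the trial gets one draw, and the two at 90:10 fall well below target.

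A reader might infer more from three places, and the documents do not support it.
- *That most draws damage the trial.* Fourteen of 20 are unbalanced, but 12 of these cost only about four points of power once month is adjusted for.
- *That a bias of up to 5.9 mm, 61% of the margin, is to be expected.* That needs month to be omitted, the 90:10 draw, and the 10-month recruitment in Trial status combined with rates that would fill the trial in under five months (134/30 = 4.5). Omitting month is a fault of the analysis, not of the draw. The draws are also symmetric, so this is chance imbalance in one realization and not bias of the procedure.
- *That {16b} would let all six hospitals start alike.* It does not say that the six picks are independent, and {16a} gives an explicit 3:3 guarantee. This is loose wording to be aligned.

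Nor does the article say that the crossover was chosen to protect against season; {16a} justifies cluster allocation by round-the-clock emergency care.

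Finally, Implementation {16c} reports the sequence as already generated, and Trial status gives a first inclusion in June 2023. The randomization remedy may therefore come too late, but the analysis and reporting remedies do not.

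**Conclusion.** The point holds as a minor one. The draw ignores hospital size, and on the plan's rates with a common switch, 10% of permitted draws give a 90:10 split and about 58% month-adjusted power at n=120. The other 90% of draws stay well above target. The 2 and 4 mm shifts apply only if the primary comparison omits month. {20a} implies that it does, while Sample size {14} says that season should be accounted for.

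The result rests on rates of which two are placeholders, and on hospitals switching at about the same time, which conflicts with a switch after 20 inclusions at each. If the two unknown hospitals recruit 4 or more per month, no draw falls below 80% power.

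**What to change.** In {16a}, draw at random only among 3:3 allocations that roughly balance expected inclusions between the two sequences. On the plan's rates this places the largest hospital opposite the two mid-size ones, which leaves 6 of the 20 allocations, each 15:15. State the rule in terms of expected inclusions and use updated rates where available: if the two unknown hospitals recruited 7 per month, 2 of those 6 allocations would be 64:36. Align the wording of {16b} with the 3:3 guarantee.

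If the draw has been made and is not redone, keep center and month in the primary model, as in the second simulation, and say so in {20a}. Report the number of patients by sequence and the resulting standard error. Reconcile the switch after 20 inclusions per hospital with the unequal rates and the total of 134.

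The cost is a few lines in the R script and a few sentences. The downside is fewer possible allocations and so a slightly more predictable sequence, in an open-label trial where {16c} says each hospital already knows its treatment in advance.
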